### 2.5 Sample size

To identify clinically meaningful improvements, responders will be defined as patients who show a FACT-Cog PCI score reduction of at least 6.5 points between baseline and M4. This threshold is based on previously validated minimal clinically important differences observed in patients with cancer, and estimated from the results of the TémoIN trial (NCT03257618) (Darlix et al., 2024) and the study by (Bray et al. 2017). A sample size of 168 evaluable patients is required to detect a 6.5-point mean difference in the FACT-Cog PCI score (control: 50, intervention: 56.5) with 80% power, two-sided α = 0.05, and an assumed standard deviation of 14 (Darlix et al., 2024; Bray et al., 2017). To take into account drop-outs, a conservative attrition rate of 10% was considered for this clinically stable LrGG population. This rate is consistent with attrition benchmarks in glioma trials, but it is likely to overestimate losses in cohorts of patients with clinically stable LrGG that are generally characterized by higher retention. Participation burden (many questionnaires at multiple time points) was also taken into account.

Therefore, 187 patients will be enrolled (187 × 0.90 = 168 patients evaluable at M4 for the primary endpoint). Based on prior observations from the TémoIN study (NCT03257618) showing that ~50% of screened patients were eligible, 374 patients will be screened over 24 months to reach the planned sample size (*n* = 187).

For the secondary endpoints, cumulative attrition is conservatively projected as follows: =10% by M6, =15% by M12, and =20% by M18. These estimates reflect modest progressive losses to follow-up, but also take into account the relative functional stability of patients with LrGG and the planned retention strategies (flexible schedule, family caregiver engagement, proactive follow-up). Sample size targets and the resulting evaluable number of patients were adjusted to align with these timepoint-specific attrition expectations, ensuring sufficient power for the primary and secondary analyses. Using these estimates, the expected number of evaluable participants at each scheduled assessment is reported in Figure 2.

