### 2.6 Randomization

Patients will be randomized in a 2:1 ratio (intervention: control) using a random block randomization method. This approach will maximize the number of patients who can benefit from the FREEDOME program. Stratification factors include:

Number of treatment lines (chemotherapy or radiotherapy, 0 vs. 1–2 vs. > 2);Baseline FACT-Cog PCI score (cognitive complaints) and HADS (distress) score (PCI score ≤ 47 and/or HADS score ≥13/42 vs. PCI score >47 and HADS score <13/42);Tumor histological grade (grade 2 vs. 3).

Investigators will register patients using the online electronic case report form (Ennov Clinical^®^).

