This approach may allow us to address both transdiagnostic emotional symptoms and specific issues encountered by patients with LrGG. Sessions will be standardized at all centers, with a minimum of three consultations and flexibility for additional sessions (up to one per week) for 4 months, depending on the patient's clinical profile. Tables 2, 3 present the CBT syllabus (overview and long version, respectively) for transparency and reproducibility.

**Table 2 T2:** CBT syllabus (overview).

**Session(s)**	**Core content**	**Theoretical framework**	**Clinical objectives**
Introductory session (mandatory)	Symptom review, therapeutic rationale, motivational enhancement, functional analysis (cognition, fatigue, sleep, emotional distress)	Unified Protocol (Barlow), CBT model of psychopathology	Build therapeutic alliance, clarify treatment goals, enhance motivation
Core sessions (≥2 mandatory; additional weekly sessions for up to 15 weeks, if clinically indicated)	Psychoeducation on emotions; assessment of cognitive distortions; cognitive restructuring; behavioral activation; fatigue- and sleep-focused strategies (CBT-I components: sleep hygiene, stimulus control, sleep restriction if needed); adaptive coping skills training	Unified Protocol (psychoeducation, cognitive restructuring, emotion regulation); CBT-I (as indicated)	Increase emotional awareness, challenge maladaptive cognitions, improve sleep/fatigue management, foster adaptive coping
Final/closure session (mandatory)	Relapse prevention, consolidation of the learned skills, recommendations for daily life and digital tool use	Unified Protocol (relapse prevention), CBT-I (maintenance)	Consolidate adaptive responses, enhance autonomy, reduce relapse risk

**Table 3 T3:** CBT syllabus (details).

**Module**	**Main objectives**	**Content/Techniques**	**Adaptations to LrGG**
1. Introduction and motivation	Assess symptoms and expectations; build alliance; enhance motivation	Motivational interviewing; goal setting; program overview	Link to cancer history and treatment experience
2. Psychoeducation on emotions	Understand adaptive role of emotions; differentiate normal vs. pathological responses	Psychoeducation; thought–emotion–behavior cycle	Applied examples: fear of progression, fatigue, irritability
3. Emotional awareness	Increase attention to emotional experience; reduce avoidance	Emotion observation; emotion journal	Adapted to cognitive limitations or impairments (guidance, visual aids)

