### 2.13 Data analysis

A statistical analysis plan will be drafted before database locking. For the for primary endpoint, all statistical analyses will be done using the intention-to-treat population and the evaluable population (i.e., patients with a FACT-Cog PCI score at baseline and M4).

Frequencies (N) and percentages (%) will be used to describe qualitative variables, and missing data reported. Percentages will be calculated after excluding missing data. Number of observations (N), median, minimum, maximum, mean, standard deviation, and interquartile range will be used to describe quantitative variables.

Baseline demographic and clinical characteristics, interventions and concomitant treatments will be described.

Questionnaire scores will be calculated according to established guidelines: FACT-Cog (Lange et al., 2016), QLQ-C30 and BN20 (EORTC manual), PRMQ (Guerdoux-Ninot et al., 2019), and neurocognitive and psychopathological tests (Gentile et al., 2003; Savard et al., 2005; Razavi et al., 1990; Beck et al., 1996; Bellaert et al., 2022; Nasreddine and Patel, 2016; Wechsler, 2011; Rieu et al., 2006; Bayard et al., 2023; Prevost et al., 2014; Spielberger, 1983; Guilmette et al., 2020). Scores will be reported and missing data rates recorded at all time points. Adherence rates will be estimated with their 95% confidence intervals.

The primary endpoint (FACT-Cog PCI score at M4) will be compared between arms with the Student's *t*-test or Wilcoxon/Mann-Whitney rank-sum test. An ANOVA or ANCOVA model will be used to adjust for potential confounders. A 5% significance threshold will be applied.

For the secondary endpoints:

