The planned trial has some limitations. First, the absence of a placebo control condition (e.g., same number of telehealth sessions with a non-specialized facilitator and non-therapeutic digital games) limits the ability to identify the specific therapeutic effects of the intervention components. The decision not to include a placebo control group in this trial reflects methodological and ethical considerations. In psychotherapy research, particularly in neuro-oncology, incidental factors (e.g., therapeutic alliance, expectations, and emotional engagement) are not inert, but rather integral to the intervention mechanisms of action (Benedetti et al., 2011; Blanco et al., 2010; Carpenter et al., 2018). Therefore, the design of placebo conditions based on alternative therapies, dismantled interventions, or minimal supportive treatments raises significant concerns. Indeed, this design carries the risk of conflating theoretical models, fails to ensure equivalence in common factors, and may not meet the ethical standards in a medically vulnerable population. In patients with LrGG, in whom cognitive and emotional impairments are clinically relevant and interrelated, a placebo condition would not offer a valid and ethically acceptable comparison. For these reasons, we opted for a real-world control group (usual care). This choice allows an ecologically valid assessment of the added value of the neuro-psychotherapeutic intervention. Non-specific factors, such as attention, perceived support or expectancy effects, may partially explain the observed benefits. The effect size between the intervention and control groups will be discussed in the light of the existing data on placebo effects. For instance, in (Carpenter et al. 2018), the odds ratio of the response rate to CBT compared to placebo was 2.97. Moreover, patients allocated to the control arm will receive standard care according to their center's standard practice. This may include a variety of interventions to reduce cognitive complaints, inducing a variability and thus a risk of bias. However, the existing shortage in Europe of professionals specialized in the cognitive and emotional assessment and management of patients with LrGG before and after surgery (Manso-Ortega et al., 2022) (and possibly even more in the long-term postoperative phase) may contribute to reduce variability within the control group.

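### With 2:1 allocation, the equal-variance Student's t-test and ordinary ANCOVA leave the primary p-value and confidence interval unprotected if the arm SDs differ; an unequal-variance analysis costs almost nothing

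*Protocol article*

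**What the plan says.** Section 2.13 names the primary comparison: "The primary endpoint (FACT-Cog PCI score at M4) will be compared between arms with the Student's" t-test, or alternatively the Wilcoxon/Mann-Whitney rank-sum test. ANOVA or ANCOVA serves for adjustment, and the threshold is 5%. The same section uses these methods for the between-arm comparison of the secondary questionnaire scores.

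Section 2.6 fixes the allocation: "Patients will be randomized in a 2:1 ratio (intervention: control) using a random block randomization method".

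Section 2.5 gives the design values. "A sample size of 168 evaluable patients is required" to detect a difference of 6.5 points (control 50, intervention 56.5) "with 80% power, two-sided α = 0.05, and an assumed standard deviation of 14". That is one SD for both arms; no arm-specific SD appears anywhere.

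The Discussion (section 3) comments on spread in the control arm, without figures. It first says that varied usual care may introduce variability, then that the shortage of specialists "may contribute to reduce variability within the control group".

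**The concern.** Student's t-test and ordinary ANOVA/ANCOVA estimate one variance for both arms. With equal arm sizes, a wrong equal-variance assumption does little harm, because the pooled standard error is still close to the true one. At 2:1 this protection is gone. The pooled variance is dominated by the larger arm, while the true variance of the difference depends most on the smaller arm. If the control arm is the more variable one, the standard error is too small and the test rejects too often. If the intervention arm is the more variable one, the standard error is too large and power is lost. The confidence interval is wrong in the same way.

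At stake is the calibration of the primary result and of every secondary score compared by these methods. Equal spread is plausible but not assured. For example, section 2.8.1 allows "flexibility for additional sessions (up to one per week) for 4 months", so exposure within the intervention arm will vary. Whether that widens or narrows the M4 scores cannot be told from the document.

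**Working it through.** **Inputs.** Difference 6.5, SD 14, two-sided alpha 0.05, 168 evaluable (section 2.5); 2:1 allocation (section 2.6). Evaluable per arm, assuming equal attrition: 168 × 2/3 = 112 intervention and 168 × 1/3 = 56 control.

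**Step 1: the plan's own figure.** Standard error = 14 × √(1/112 + 1/56) = 2.291. Noncentrality = 6.5 / 2.291 = 2.837. With 166 degrees of freedom the critical value is 1.974, and the noncentral t distribution gives a power of 80.5%. The normal-approximation sample size is 55 + 110 = 165, close to the 168 stated. The design reproduces under its own assumption.

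**Step 2: why 2:1 matters.** With intervention SD s₁ (n₁ = 112) and control SD s₂ (n₂ = 56):

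- expected pooled SE² = [(111 s₁² + 55 s₂²) / 166] × (1/112 + 1/56)
- true SE² = s₁²/112 + s₂²/56

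Example 12/16 (intervention/control): pooled variance = (111 × 144 + 55 × 256) / 166 = 181.1, so pooled SE = √(181.1 × 0.02679) = 2.203. True SE = √(144/112 + 256/56) = 2.420. The ratio is 0.91, so the standard error is about 9% too small.

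Example 16/12: pooled variance = (111 × 256 + 55 × 144) / 166 = 218.9, so pooled SE = 2.421. True SE = √(256/112 + 144/56) = 2.204. The ratio is 1.10, so the standard error is about 10% too large.

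**Step 3: size and power by simulation.** Normal data, 112 and 56, two-sided 5%, 6.5-point effect for power. Where repeated runs (up to 200,000 replicates) differed in the last digit, the range is shown. All unequal SD pairs are assumptions.

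| SD intervention/control | Student size | Welch size | Student power | Welch power |
|---|---|---|---|---|
| 14/14 (plan) | 4.9–5.0% | 4.9–5.0% | 80.6–80.7% | 80.4% |
| 15/13 | 4.0–4.1% | 5.0% | 79.7% | 82.1% |
| 13/15 | 6.1–6.2% | 4.9% | 81.3% | 78.4% |
| 16/12 | 3.1–3.2% | 5.0–5.1% | 78.1–78.2% | 83.3–83.4% |
| 12/16 | 7.4–7.6% | 4.9–5.1% | 81.2–81.4% | 75.6–75.8% |

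For 13/15 and 12/16, Student's higher power is bought with the inflated size.

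**Step 4: confidence interval.** For normal data the coverage of the 95% interval is 100% minus the size, whatever the true difference. At 12/16 it is about 100 − 7.6 = 92.4%; at 16/12, about 100 − 3.1 = 96.9%.

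**Step 5: the one numeric hint of heterogeneity in the text.** Section 2.3 cites mean changes of 16.3 and 12.6 points above and below 25 h of training, a gap of 3.7. If half the intervention arm falls on each side (assumption), its SD becomes √(14² + 0.25 × 3.7²) = √199.4 = 14.12. Student's size is then 5.0% and its power 80.0%. This figure alone causes no problem.

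**The case against.** A reader might infer that the plan itself predicts different spread in the two arms, so that its 5% and 80% fail. The document does not support this. The Discussion raises extra control-arm variability and then partly discounts it, and it never compares the two arms. Flexible session numbers do not imply a wider outcome, since effort directed by clinical profile could equally narrow it. One therapist works from a supervised manual (sections 2.8.1 and 2.12). The only SD is a common 14, under which the stated figures reproduce, and the one numeric hint of heterogeneity barely moves them.

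It is also true that if the programme changes no patient's score relative to usual care, randomised arms share one distribution and the 5% level holds. The size figures above concern equal means with unequal spread. The coverage and power consequences remain whenever a real but uneven effect changes the spread.

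The last objection is that pooled versus unequal variance belongs in the statistical analysis plan, which section 2.13 says will be drafted before database lock. This carries weight for severity. But the article does not leave the test open on this point: it names Student's, and an analysis plan that follows it would inherit the equal-variance assumption.

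**Conclusion.** The point holds as a method choice that can be improved, not as an error in the stated design. Under the common SD of 14 the trial has its 5% level and about 80% power. If the SDs differ, Student's test and ordinary ANOVA/ANCOVA are miscalibrated at 112 and 56: size about 4.1% and 6.2% for intervention/control SDs of 15/13 and 13/15, and about 3.1% and 7.6% for 16/12 and 12/16. These pairs are assumed, as are normality and equal attrition. The document supplies neither arm-specific SDs nor a direction, so no claim can be made that inflation, or loss of power, will occur. The unknown direction is itself the reason to prefer a method that is valid in both cases. Severity is modest.

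**What to change.** In section 2.13, and in the analysis plan, name Welch's unequal-variance t-test for between-arm comparisons in place of Student's. In the ANOVA/ANCOVA, use heteroscedasticity-robust standard errors (for example HC3) or arm-specific residual variances. Apply the same to the secondary scores.

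The change takes a sentence or two and needs no patients or data. If the SDs are equal, it costs about 0.3 points of power (80.7% to 80.4%). If the control arm is the more variable one, power will be lower than Student's nominal figure (for example 75.6–75.8% against 81.2–81.4% at 12/16), but at a correct 5% level. If the intervention arm is the more variable one, power is recovered (83.3–83.4% against 78.1–78.2% at 16/12). The change should be made before any outcome data are seen by arm.

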### 2.2 Study objectives

The primary objective is to assess the impact of the FREEDOME program on the perceived cognitive impairment in patients with LrGG at month 4 (M4) after the intervention. Secondary objectives include assessing the patient adherence, and evaluating the intervention effect on subjective cognitive and memory complaints, HRQoL (particularly, sleep, fatigue, return-to-work) and psychological problems at M4, M6, M12 and M18 after the intervention. The study will also assess neurocognitive functioning at baseline, M4 and M12, and investigate the relationship between subjective and objective cognitive outcomes. Lastly, exploratory objectives will focus on evaluating the longitudinal impact of the intervention on memory and irritability as perceived by family caregivers at M4, M6, M12, and M18.

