Patient adherence (i.e., completing at least 25 h of the recommended 40 h of the digital program and attending three telehealth consultations). The 25-h threshold is based on the study by (Bray et al. 2017), where the FACT-Cog PCI score change was higher in participants who trained >25 h than in those who trained <25 h (16.3 vs. 12.6 points). The three telehealth sessions (at the intervention start, mid-point, and end) will ensure sufficient therapeutic support, address barriers, and will allow reviewing progress and delivering personalized recommendations.Comparison of the FACT-Cog PCI scores (Lange et al., 2016) at baseline, M6, M12, and M18.Comparison of the scores the three other FACT-Cog subscales at baseline, M4, M6, M12, and M18.Comparison of the Prospective and Retrospective Memory Questionnaire (PRMQ) scores (Guerdoux-Ninot et al., 2019) at baseline, M4, M6, M12, and M18.Comparison of the EORTC QLQ-C30 scores (Aaronson et al., 1993) and its module Brain-20 (BN20) scores (Taphoorn et al., 2010) at baseline, M4, M6, M12, and M18.Comparison of the 20-item Multidimensional Fatigue Inventory (MFI-20) (Gentile et al., 2003) and the Insomnia Severity Index (ISI) (Savard et al., 2005) scores at baseline and M4, M6, M12, and M18.Proportion of patients returning to work or increasing their work hours at M4, M6, M12, and M18.Changes in self-rated psychological distress, depression, anxiety and irritability between baseline and M4, M6, M12, and M18 using the Hospital Anxiety and Depression Scale (HADS) (Razavi et al., 1990), Beck Depression Inventory-II (BDI-II) (Beck et al., 1996), State-Trait Anxiety Inventory-Y (STAI-Y) (Bellaert et al., 2022), and Brief Irritability Test (BITe) (Bellaert et al., 2022), respectively.Differences (between baseline and M4 and M12) in the clinician-rated scores of the following neurocognitive tests: Montreal Cognitive Assessment (MoCA) (Nasreddine and Patel, 2016), Working Memory Index [score derived from the Digit Span and Arithmetic subtests of the Wechsler Adult Intelligence Scale, Fourth Edition (WAIS-IV)], Processing Speed Index (from the Coding and Symbol Search subtests of the WAIS-IV) (Wechsler, 2011), Hopkins Verbal Learning Test (global scores) (Rieu et al., 2006), Standard Executive Neuropsychological Test Battery (Bayard et al., 2023) (including the modified Stroop Delis-Kaplan test, the Digit Span subtest of the WAIS-IV, the Verbal Fluency Test, the Trail Making Tests A and B), and Reading the Mind in the Eyes Test (Prevost et al., 2014).Correlations between the FACT-Cog sub-scores or PRMQ scores and key neurocognitive domains (global functioning, executive functions, language, working memory, processing speed, and social cognition) at baseline, M4, and M12.

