#### 2.8.2 BrainHQ digital application

The Brain HQ digital application (Insight from Posit Science Brain HQ, San Francisco, California, USA) is a digital neurocognitive training program designed based on the principles of neuroplasticity. It was developed by an international team of neuroscientists led by [name] with the objective of improving cognitive functions through structured exercises. Participants will train for 60–160 min per week, divided into 1–4 sessions of 40–60 min/each. The recommended training regimen consists of four 40-min sessions per week for 15 weeks (total = 40 h). A detailed overview of the exercises included in the application is provided in Table 4.

**Table 4 T4:** Detailed description of the BrainHQ digital program.

**Exercise**	**Content**
Double decision	This module leverages a unique, proven technology designed to accelerate processing speed and expand the useful field of vision. Commonly referred to as “speed training” in research, this technology has been used in many studies that demonstrate benefits such as faster visual processing, broader field of view, enhanced driving safety, and more.
Follow the target	Participants are required to divide their visual attention and track multiple moving objects simultaneously. The target tracker is designed to encourage patients to divide their focus by challenging them to follow several objects that move at the same time on the screen.
Visual scanning	This module trains patients to identify without effort specific visual patterns at high speeds, enhancing their overall visual acuity. The key skill targeted by this module is visual processing speed. During the exercise, the color, direction, and thickness of the scanning bars will vary to challenge the participants.
Attention to detail	Designed to improve patients' ability to make quick, precise saccades, this module trains the ability to notice subtle details with each eye movement. It focuses on quickly and reliably extracting information from each visual fixation.
Hawk eye	This module enhances visual accuracy, enabling patients to see details rapidly and precisely. This improves memory encoding, allowing patients to better retain the information they encounter (e.g., from a film, a wedding, house hunting, birdwatching). The ability to remember these details accurately helps them to discuss these experiences effectively in the future. The aim of this module is to improve everyday life activities.

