- the FACT-Cog PCI scores will be compared between arms and time points using a similar method. A 5% significance threshold will be applied with adjustments for multiple comparisons to control the alpha risk using the Benjamini–Hochberg method (Benjamini and Hochberg, 1995). All exploratory analyses will be performed without adjustment.- Partial correlations between the FACT-Cog or PRMQ subscale score and key cognitive domains will be evaluated using Spearman or Kendall Tau correlation coefficients, adjusted for distress (HADS) and fatigue (MFI-20, ISI). Each neuropsychological threshold will be defined according to the test guideline and taking into account many variables, such as age, sex and/or socio-cultural level.- Other questionnaire scores will be compared between arms with the Student's *t*-test or Wilcoxon/Mann-Whitney rank-sum test. An ANOVA or ANCOVA model will be used to adjust for potential confounders.

Within each arm, score differences (HADS, PRMQ, BDI-II, STAI-Y, BITe, MFI-20, ISI, QLQ-C30, and BN20) between baseline and the subsequent timepoints will be assessed using the paired Student's *t* or Wilcoxon signed-rank test.

First, the mean score change over time will be graphically represented using the LOcally Estimated Scatterplot Smoothing method (LOESS).

Then, Linear Mixed Models (LMMs) may be used to model the score changes over time in function of the group. These LMMs will include random intercepts and slopes, assuming a linear trajectory over time. If necessary, more flexible LMMs (e.g., spline-based models) may be considered.

Although the open-label design may expose the study to attention and expectancy biases, particularly regarding self-reported outcomes, the data analysts involved in the primary outcome analysis will remain blinded to group allocation.

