In some previous trials, control groups were matched based on neuropsychological test scores rather than cognitive complaints or relevant psychopathological variables (Richard et al., 2019). This is an issue because neuropsychology studies (cancer-related or not) (Guerdoux et al., 2009; Paquet et al., 2017; Tucha et al., 2000) frequently report dissociation between the patient-reported neurocognitive problems and the objective performance. By focusing on the perceived cognitive impairment as the primary outcome, this study is in line with growing evidences that subjective complaints are clinically meaningful, often predictive of psychological distress, and may not always correlate with objective deficits. Unlike previous studies that lacked control groups (Maschio et al., 2015; Hassler et al., 2010), our randomized design should allow determining the real impact of the hybrid rehabilitation intervention on the perceived cognitive impairment. This may also help to guarantee sufficient insight and motivation to engage with the intervention. Moreover, the collection of subjective and objective data over time should allow a more nuanced understanding of the relationship between the patients' experiences and their objective neurocognitive performance. In parallel, evaluating adherence, fatigue, psychopathological symptoms, and caregiver-reported outcomes will provide insights into the broader systemic impact of the intervention.

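### The partial correlations between complaints and test performance at M4 and M12 do not list randomised arm as a covariate; if the arms are pooled, a programme effect on both measures can add a small between-arm component

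*Protocol article*

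**What the plan says.** A secondary objective in section 2.2 is to "investigate the relationship between subjective and objective cognitive outcomes". Section 2.3 lists the matching endpoint, "Correlations between the FACT-Cog sub-scores or PRMQ scores and key neurocognitive domains", with the domains and times given as "global functioning, executive functions, language, working memory, processing speed, and social cognition) at baseline, M4, and M12".

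Section 2.13 gives the method: "Partial correlations between the FACT-Cog or PRMQ subscale score and key cognitive domains will be evaluated using Spearman or Kendall Tau correlation coefficients". The covariate list that goes with this method has three scales on it and reads "adjusted for distress (HADS) and fatigue (MFI-20, ISI"). No other covariate is named for this analysis, and no sentence says whether the coefficients are computed over all patients or by arm. Elsewhere the same section is explicit about arm. The score comparisons are between arms, and the paired changes are introduced with "Within each arm, score differences (HADS, PRMQ, BDI-II, STAI-Y, BITe, MFI-20, ISI, QLQ-C30, and BN20").

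Allocation is 2:1 in favour of the programme (section 2.6). Baseline testing precedes randomisation (section 2.7), so only the M4 and M12 correlations are computed on a mixture of treated and control patients.

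**The concern.** The plan partials out distress and fatigue because they could drive both complaints and test scores. After randomisation, arm may be another such common cause. The programme is meant to improve perceived cognitive impairment. Table 4 in section 2.8.2 describes one training module as "designed to accelerate processing speed and expand the useful field of vision", and processing speed is one of the domains to be correlated. If both shift, treated patients sit higher on both scales and controls lower. A pooled coefficient then contains a between-arm component even when complaints and performance are unrelated within each arm.

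At stake is the reading of a secondary analysis on how far complaints track performance. The extra component is in one direction, is absent at baseline, and can arise only if the programme moves both measures.

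**Working it through.** **Inputs from the protocol article**
- Planned PCI difference 6.5 points, SD 14, 80% power, two-sided 5%, 168 evaluable patients at M4, 187 enrolled (section 2.5).
- Share of patients in the programme arm p = 2/3, so p(1−p) = 2/9 (section 2.6).
- Attrition of 15% by M12 (section 2.5): 187 × 0.85 ≈ 159.

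**Assumptions not in the article**
- The effect on a test score, d2 (in SD), is varied from 0 to 0.8.
- The within-arm correlation is zero, both scores are coded so that higher is better, and each correlation gets a nominal 5% two-sided test.
- The PCI effect is planned for M4 only; carrying it to M12 is an assumption.

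**Step 1: the plan's own figure.** With 2:1 allocation, the control-arm size is 1.5 × (1.960 + 0.842)² × 14² / 6.5² = 54.6, so 55 controls and 165 in total, close to the stated 168. With 56 and 112 patients the power is 0.81. Also, 187 × 0.90 = 168.3. The sample size reproduces.

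**Step 2: induced correlation.** With d1 = 6.5/14 = 0.464,

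r = p(1−p)·d1·d2 / √[(1 + p(1−p)·d1²)(1 + p(1−p)·d2²)].

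For d2 = 0.464: (2/9)(0.2156) = 0.0479, and r = 0.0479/1.0479 = 0.046.

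**Step 3: rejection rate.** With three covariates, Fisher's z has standard error 1/√(168 − 3 − 3) = 0.079, so r = 0.046 is about 0.6 standard errors.

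| Assumed d2 | Induced r | Rejection, n = 168 |
|---|---|---|
| 0 | 0 | 5.0% |
| 0.2 | 0.020 | 5.8% |
| 0.3 | 0.030 | 6.7% |
| 0.464 | 0.046 | 9.0% |
| 0.5 | 0.049 | 9.6% |
| 0.8 | 0.075 | 16.1% |

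At n = 159 and d2 = 0.464, r is again 0.046 and rejection is 8.7%.

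**Step 4: simulated partial Spearman, three scales adjusted for, arm omitted, n = 168.** When the scales do not respond to the programme, two separate simulations bracket the table:
- d2 = 0.30: 6.3% and 6.6%.
- d2 = 0.464: 8.6% and 9.0%.
- d2 = 0.80: 15.7% and 17.8%.

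When the scales respond as well and are related to complaints, the component shrinks:
- Scales shifted by 0.3 SD, d2 = 0.464: mean r = 0.032, rejection 7.2%. With a stronger assumed relation (0.6) between the scales and complaints: r = 0.028, rejection 6.9%.
- Under that stronger relation, scales shifted by 0.3 SD with d2 = 0.3: 5.1%. Scales shifted by 0.46 SD with d2 = 0.46: 5.2%.

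**Step 5: arm added as a covariate.** Mean r lies between −0.003 and 0.001, and rejection between 4.4% and 5.7% in every scenario, which is nominal within simulation error.

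**The case against.** **Pooling is inferred.** A reader might infer that the article prescribes pooled correlations. It does not say so. Pooling is the natural reading because arm is written out for other analyses and not here, but by-arm analysis is not excluded. The article condenses a longer protocol, and section 2.13 says that an analysis plan is still to be drafted. This stands as a limit on the wording. It does not dispose of the point, because a covariate set is stated, and an analysis that follows it as written leaves out arm.

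**No comparison over time is planned.** It is tempting to say that the trial would wrongly conclude that complaints became more tied to performance after treatment. The article plans no test of change in the correlations. The Discussion's remark that "the collection of subjective and objective data over time should allow a more nuanced understanding" is general and sets no analysis. What remains is a possible shift in single cross-sectional coefficients at M4 and M12.

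**Few domains are exposed.** A reader might extend the point to attention, which Table 4 also trains. Attention is not among the six correlation domains in section 2.3. Of those six, only processing speed is plainly a training target. Where the programme does not move a domain, the component is exactly zero. Nor is any effect planned for a cognitive test, for the PRMQ or for the other FACT-Cog subscales.

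**The planned covariates do part of the work.** The therapy sessions address emotion regulation, fatigue and sleep (section 2.8.1), so HADS, MFI-20 and ISI may carry part of the arm effect. This is right, and step 4 shows rejection falling to about 5 to 7%. They substitute for arm only so far as the programme acts through them.

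**A pooled coefficient is not false.** If treatment improves both measures, better performers at M4 do report fewer complaints, and a pooled coefficient describes that mixture correctly. Section 2.2 does not say which association is wanted. But the plan already removes common causes, which points to the association net of them, and a pooled value also depends on the 2:1 allocation.

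**Conclusion.** The point holds as a minor flaw in a stated secondary method. If the arms are pooled, omitting randomised arm at M4 and M12 can add about 0.02 to 0.05 to a complaint–performance correlation, at the planned PCI effect and assumed test-score effects of 0.2 to 0.5 SD. The false-positive rate of a nominal 5% test is then 5.8% to 9.6%, and nearer 5 to 7% if the three adjusting scales also respond. About 16% needs an assumed test-score effect of 0.8 SD, larger than the trial's planned primary effect.

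The conclusion rests on pooling, on the programme affecting both measures, and on test-score effects that the article does not give. The documents do not support a claim that the plan necessarily creates a spurious correlation. Baseline correlations, the primary endpoint, the sample size and the between-arm comparisons are unaffected.

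**What to change.** In section 2.13, add randomised arm to HADS, MFI-20 and ISI as a covariate of the M4 and M12 partial correlations, or compute these correlations within arm and combine them. In either case show the arm-specific coefficients. Leave the baseline correlations as planned.

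The cost is one phrase and one degree of freedom per correlation (at n = 168, the Fisher denominator goes from 162 to 161), with no new data. The arm-specific coefficients should carry intervals, because the control arm is small: with 56 patients and three covariates the standard error is 1/√(56 − 6) = 0.14.
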